#### Dose specifications

Both hypofractionated and conventional fractionated radiation therapy are permitted: the conventional fractionated regimen is 50 Gy in 25 fractions of 2 Gy; the hypofractionated schedule is 42.5 Gy in 16 fractions of 2.67 Gy. Tumor bed or scar boost is at the discretion of the treating physician, boost doses will be 10 ~ 16 Gy in 5 ~ 8 fractions of 2 Gy, for total cumulative doses of 60 ~ 66 Gy.

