#### Technique factors and treatment planning

3D-conformal radiation therapy (3D-CRT) techniques are not recommended due to significant incidental irradiation of the SCL region. Advanced intensity modulated radiation therapy (IMRT), volumetric modulated arc therapy (VMAT), or tomotherapy techniques are recommended instead. Methods to minimize the cardiac exposure such as gating or breath-holding are permitted per treating physician’ discretion.

Suggested PTV compliance criteria are as follows: at least 95% of each PTV receives ≥ 95% of the prescribed dose (it is acceptable if ≥ 95% of each PTV receives ≥ 90% of the prescribed dose, except for PTV_IMN, it is acceptable if ≥ 90% of the PTV_IMN receives ≥ 90% of the prescribed dose); the maximum point dose (volume that is 0.03 cm^3^) is recommended to be ≤ 115% of the prescription dose (≤ 120% acceptable), and should be evaluated without the contribution of the boost fields; ≤ 35% of the PTV_B_EVA, PTV_CW_EVA, or PTV_IMN receives 100% of the boost prescribed dose when a boost is included in the composite plan (≤ 40% acceptable); ≤ 5% of the PTV_TB_EVA receives ≥ 110% of the boost prescribed dose (≤ 10% acceptable).

The OARs dose constraints are shown in Table 2.

**Table 2 Tab2:** Suggested dose constraints of organs at risk

	Conventional fractionated RT (50 Gy in 25 fractions)		Hypofractionated RT (42.56 Gy in 16 fractions)	
	required	acceptable	required	acceptable
Heart(Left_sided)	Dmean ≦ 6 Gy	Dmean ≦ 8 Gy	Dmean ≦ 5.1 Gy	Dmean ≦ 6.8 Gy
	V20Gy ≦ 5%	V25Gy ≦ 5%	V17Gy ≦ 5%	V21Gy ≦ 5%
Heart(Right_sided)	Dmean ≦ 2 Gy	Dmean ≦ 3 Gy	Dmean ≦ 1.7 Gy	Dmean ≦ 2.6 Gy
	V20Gy ≦ 0%	V25Gy ≦ 0%	V17Gy ≦ 0%	V21Gy ≦ 0%
Ipsilateral Lung	V20Gy ≦ 30%	V20Gy ≦ 35%	V17Gy ≦ 30%	V17Gy ≦ 35%
	V5Gy ≦ 60%	V5Gy ≦ 70%	V4.2 Gy ≦ 60%	V4.2 Gy ≦ 70%
Contralateral lung	V5Gy ≦ 10%	V5Gy ≦ 15%	V4.2 Gy ≦ 10%	V4.2 Gy ≦ 15%
Contralateral breast	V5Gy ≦ 10%	V5Gy ≦ 15%	V4.2 Gy ≦ 10%	V4.2 Gy ≦ 15%
Thyroid	Dmean ≦ 25 Gy	Dmean ≦ 26.2 Gy	Dmean ≦ 21.2 Gy	Dmean ≦ 22.2 Gy
Esophagus	V20Gy ≦ 10%	V20Gy ≦ 15%	V17Gy ≦ 10%	V17Gy ≦ 15%
Spinal cord	Dmax ≦ 45 Gy		Dmax ≦ 38.2 Gy	
Humeral head	Dmean ≦ 25 Gy	Dmean ≦ 26.2 Gy	Dmean ≦ 21.2 Gy	Dmean ≦ 22.2 Gy
	V30Gy ≦ 30%	V30Gy ≦ 35%	V28.5 Gy ≦ 30%	V28.5 Gy ≦ 35%
Brachial plexus	Dmax ≦ 54 Gy	Dmax ≦ 56.7 Gy	Dmax ≦ 46 Gy	Dmax ≦ 48.3 Gy

V_XXGy_ ≦YY%: the volume of each organs at risk receiving XXGy should be no more than YY%

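### Table 2's hypofractionated humeral-head volume limit (V28.5 Gy) is 0.95 of the conventional limit; all 25 other pairs are scaled by about 0.85

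*Protocol article*

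**What the plan says.** Under Dose specifications, the protocol article states that "Both hypofractionated and conventional fractionated radiation therapy are permitted". It adds that "the conventional fractionated regimen is 50 Gy in 25 fractions of 2 Gy" and that "the hypofractionated schedule is 42.5 Gy in 16 fractions of 2.67 Gy".

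Table 2, under Technique factors and treatment planning, is captioned "Suggested dose constraints of organs at risk". Each schedule has a required and an acceptable column, and the hypofractionated columns are headed 42.56 Gy in 16 fractions. For the humeral head there are two rows:

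- Mean dose: "Humeral head Dmean ≦ 25 Gy Dmean ≦ 26.2 Gy Dmean ≦ 21.2 Gy Dmean ≦ 22.2 Gy".
- Volume: "V30Gy ≦ 30% V30Gy ≦ 35% V28.5 Gy ≦ 30% V28.5 Gy ≦ 35" (the last figure is a percentage).

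The article does not say how the conventional limits were converted and gives no separate reason for the 28.5 Gy figure.

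**The concern.** The two humeral-head rows treat the same organ differently. Moving from the conventional to the hypofractionated columns, the mean-dose limits fall by about 15%, as limits do throughout the table. The dose level of the volume limit falls by only 5%, with the permitted volumes unchanged at 30% and 35%.

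Suppose the same dose distribution is delivered on either schedule. A conventional plan is judged on the volume inside the 60% isodose, and a hypofractionated plan on the volume inside the 67% isodose, which cannot be larger. The hypofractionated plan therefore passes more easily.

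This row is relevant to the trial's own questions. The Background section singles out shoulder function and pain among the toxicities to be studied, upper-limb function by q-DASH is a secondary endpoint, and the Discussion expects the larger target volume to raise shoulder dose. What is at stake is consistent protection of the shoulder across the two schedules. The efficacy comparison is not at stake.

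**Working it through.** **Inputs.** All dose limits are from Table 2. The schedules are from Dose specifications and the Table 2 header. No alpha/beta value is given in the article, so every value below is an assumption.

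**1. Prescription ratio.** 42.56/50 = 0.8512. With the 42.5 Gy printed in the text it is 42.5/50 = 0.850. The choice does not affect the result.

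**2. Ratio of hypofractionated to conventional limit, all 27 pairs.**

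| Conventional → hypofractionated (Gy) | Where | Pairs | Ratio |
|---|---|---|---|
| 6 → 5.1; 8 → 6.8; 2 → 1.7 | heart mean dose | 3 | 0.850 |
| 3 → 2.6 | right-sided heart mean dose, acceptable | 1 | 0.867 |
| 20 → 17 | heart (2), ipsilateral lung (2), esophagus (2) | 6 | 0.850 |
| 25 → 21 | heart volume, acceptable | 2 | 0.840 |
| 5 → 4.2 | both lungs (4), contralateral breast (2) | 6 | 0.840 |
| 25 → 21.2 | thyroid, humeral-head mean dose | 2 | 0.848 |
| 26.2 → 22.2 | thyroid, humeral-head mean dose | 2 | 0.847 |
| 45 → 38.2 | spinal cord | 1 | 0.849 |
| 54 → 46; 56.7 → 48.3 | brachial plexus | 2 | 0.852 |
| **30 → 28.5** | **humeral-head volume** | **2** | **0.950** |

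**3. Distance from exact scaling.** Among the 25 consistent pairs the largest gap is 25 × 0.8512 = 21.28 against 21, or 0.28 Gy, which is rounding. For the humeral-head volume cells, 30 × 0.8512 = 25.54 against 28.5. The gap is 2.96 Gy, and 2.96/25.54 = 12%. Rounding cannot explain it.

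**4. Share of prescription.** Conventional: 30/50 = 60%. Hypofractionated as printed: 28.5/42.56 = 67%.

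**5. Could 28.5 Gy be a biological conversion?** In the linear-quadratic model, a dose c in 25 fractions and a dose h in 16 are equivalent when c²/25 + (α/β)c = h²/16 + (α/β)h. Hence α/β = (h²/16 − c²/25)/(c − h).

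- Humeral-head volume: (50.77 − 36)/1.5 = 9.8 Gy.
- Humeral-head mean dose: (28.09 − 25)/3.8 = 0.8 Gy, and (30.80 − 27.46)/4 = 0.8 Gy.
- Highest among the other 25 pairs (brachial plexus, 56.7 and 48.3): (145.81 − 128.60)/8.4 = 2.05 Gy.

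No single α/β reproduces both humeral-head rows.

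**6. Excess over biological equivalence.** Setting c = 30 and solving for h gives h = 8 × [−α/β + √((α/β)² + (36 + 30 α/β)/4)].

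| Assumed α/β (Gy) | Equivalent 16-fraction dose (Gy) | Excess of 28.5 (Gy) |
|---|---|---|
| 2 | 26.3 | 2.2 |
| 3 | 26.9 | 1.6 |
| 4 | 27.3 | 1.2 |
| 5 | 27.6 | 0.9 |
| 10 | 28.5 | 0.0 |

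**7. The same comparison as EQD2 at α/β = 3 Gy.** EQD2 = D(D/n + 3)/5.

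- 30 Gy in 25 fractions: 30 × 4.2/5 = 25.2 Gy.
- 28.5 Gy in 16: 28.5 × 4.781/5 = 27.2 to 27.3 Gy.
- 25.5 Gy in 16: 25.5 × 4.594/5 = 23.4 Gy.

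**The case against.** The strongest reply is that nothing has been shown to be miscalculated. The table states no conversion rule, 28.5 Gy appears in both cells, and a conversion at an alpha/beta near 10 Gy would give that figure. A condensed article may also leave the derivation to the full protocol. It is true that intent cannot be read from the article. But an alpha/beta near 10 Gy is used nowhere else in the table, not even for the same organ's mean dose, so a deliberate exception would need a stated basis.

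Second, an organ mean dose cannot strictly be converted by the linear-quadratic model without its dose distribution, so the implied 0.8 Gy is not a real tissue parameter. That stands. It serves here only to show that the two rows were not derived in the same way, and the ratios alone already show this.

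Third, 25.5 Gy is not the biologically equivalent dose either. At an alpha/beta of 3 Gy it is 26.9 − 25.5 = 1.4 Gy too strict, while 28.5 Gy is 1.6 Gy too loose. The two are equally far off when the equivalent dose is 27 Gy: 27²/16 − 36 = 9.56, and 9.56/(30 − 27) gives an alpha/beta of 3.2 Gy. Above that value the printed figure is the closer one. This stands as a limit on the remedy: 25.5 Gy restores consistency within the table and errs toward protection, but it is not shown to be the correct tolerance dose.

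Fourth, the 28.5 Gy threshold is lower than 30 Gy in absolute dose, and the limits are only suggested. Both are true. The limit is looser as a share of prescription, and biologically for any alpha/beta below about 9.8 Gy. The columns are headed required and acceptable, so planners will work to the printed figure.

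**Conclusion.** The point holds. The two hypofractionated humeral-head volume cells do not follow the scaling of the rest of Table 2. The printed threshold is about 3 Gy (12%) above the value that this scaling gives. This part needs only the table's own figures and the inference that the other 25 pairs reveal the rule.

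The biological excess is smaller and conditional: 2.2 Gy at an assumed alpha/beta of 2 Gy, 1.6 Gy at 3 Gy, 0.9 Gy at 5 Gy, and none near 10 Gy. A slip of 0.95 for 0.85 would produce exactly 28.5 Gy, but the article cannot prove that this happened.

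The practical effect is modest. Only a hypofractionated plan that meets the mean-dose limit, and whose humeral-head volume passes at 28.5 Gy but fails at 25.5 Gy, would be judged differently. The article gives neither dose-volume data nor the share of patients on the hypofractionated schedule, so the number of such plans is unknown and may be small. Both arms use the same table, so the primary analysis, the sample size and the fairness of the comparison are untouched. It should be corrected because it is a planning threshold in use while accrual continues, in a trial that studies shoulder toxicity.

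**What to change.** Change the two cells to V25.5 Gy, keeping ≦ 30% as required and ≦ 35% as acceptable. If 28.5 Gy is deliberate, keep it and state the basis for this one limit in a table footnote. Check the operational protocol, and send sites a short notice if it carries the same figure.

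The cost is two table cells or one footnote, plus the notice if needed. Some hypofractionated plans may take slightly more planning effort. At an assumed alpha/beta of 3 Gy the corrected limit is also somewhat stricter than the conventional one (EQD2 23.4 against 25.2 Gy). The organ's mean-dose row already has this property: treating 25 Gy as a uniform dose, the equivalent in 16 fractions is 8 × (−3 + √34) = 22.65 Gy, against the printed 21.2 Gy.

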#### Treatment verification

Before the first time of radiotherapy, portal films or 3D-CRT images (e.g., conebeam CT, MV CT, kV CT) must be obtained and approved by a physician. During radiotherapy, portal films or 3D-CRT images must be obtained every 5 fractions.

### Follow-up

During radiotherapy, patients will attend the clinic every 2 weeks and at the end of treatment. Physical examination, hematology tests, and acute radiation toxicity (including acute radiation dermatitis, pneumonitis, esophagitis, neck and should pain, and myocardial ischemia/infarction) will be performed.

After completing radiotherapy, efficacy assessments for recurrence, new cancers and overall survival will be conducted every 3 months for the first 2 years, every 6 months for the years 3 ~ 5, and then annually until 10 years from randomization. Efficacy follow-up includes symptoms assessment, physical examination, hematology tests, blood chemistry/tumor-markers tests, Ultrasounds, mammogram annually, and chest CT scans annually. Breast magnetic resonance imaging (MRI) is permitted in doubtful cases. Additional imaging such as positron emission tomography /computed tomography (PET/CT), bone emission computed tomography (ECT), brain MRI, or biopsy will be performed as indicated for suspected recurrence or metastasis. Acute radiation adverse events will be assessed until 3 months after completing radiotherapy. Late radiation adverse events will be assessed starting at 3 months after completing radiotherapy and then annually. The follow-up workflow is shown in Table 3.

**Table 3 Tab3:** Follow-up workflow

	Baseline	During RT	End of RT	First 2 years after RT	3 ~ 5 years after RT	Beyond 5 years after RT
		Every 1 ~ 2 week		Every 3 months	Every 6 months	Every 12 months
Clinical examination	X	X	X	X	X	X
Hematology tests	X	X	X	X	X	X
Blood chemistry/tumor-markers tests	X			X	X	X
Ultrasounds	X			X	X	X
Mammogram	X			every 12 months after RT		
Chest CT*	X			every 12 months after RT		
Acute radiation adverse events	X	X	X	At 2 weeks and 3 month after RT		
Late radiation adverse events	X			At 3 month after RT, and than every 12 months		
PROs/QoL questionnaires	X			At 3 month after RT, and than every 12 months		
Blood biomarker samples	X		Carried out if possible			

* Additional imaging such as positron emission tomography /computed tomography (PET/CT), bone emission computed tomography (ECT), brain (MRI), or biopsy will be performed as indicated for suspected recurrence or metastasis

Abbreviations: RT = radiation therapy; CT = computer tomography; MRI = magnetic resonance imaging; PROs = patient reported outcomes; QoL = quality of life

### Sample size and statistical analysis

The primary endpoint is DFS. According to data from a Chinese prospective study, the 5-year DFS for high-risk patients after breast-conserving surgery or mastectomy is 73% [19] (control group). We assume a clinically meaningful difference in 5-year DFS of 5% between groups. The hypothesis of the current study is that the 5-year DFS will be superior in the E-SCLI group (experiment group) compared to the M-SCLI group (control group), with a 5-year DFS increase from 73% in the M-SCLI group to 78% in the E-SCLI group. Sample size calculation for comparing DFS was performed with a two-sided α = 0.05 and 80% power. Hazard ratio is 0.79. This yields to a total sample size of 1500 patients. Accounting for a 10% dropout rate, the total sample size is increased to 1650 patients (825 per group). Based on these assumptions, it is estimated that 510 events will be required for the final analysis. Statistical analysis will be performed based on the intent-to-treat principle, with all patients analyzed as randomized, regardless of eligibility or protocol compliance.

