### Randomization

Eligible patients will be centrally randomized in a 1:1 ratio to the M-SCLI group and the E-SCLI group. Randomization will be stratified according to the following factors: neoadjuvant systemic therapy vs. adjuvant systemic therapy; T3-4 vs. T1-2; N3 vs. non-N3; ER positive vs. ER negative.

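### The 510 DFS events said to be required give about 76% power, not the stated 80%; the plan's own inputs need about 562 to 566.

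*Protocol article*

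**What the plan says.** The relevant text is in the protocol article under Sample size and statistical analysis. The endpoint is DFS, and the hypothesis is superiority of entire over medial supraclavicular irradiation, "with a 5-year DFS increase from 73% in the M-SCLI group to 78% in the E-SCLI group". The error rates are fixed: "Sample size calculation for comparing DFS was performed with a two-sided α = 0.05 and 80% power". The effect size follows: "Hazard ratio is 0.79". Allocation is given under Randomization: "Eligible patients will be centrally randomized in a 1:1 ratio to the M-SCLI group and the E-SCLI group".

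The section derives 1500 patients, raises this to 1650 (825 per group) for 10% dropout, and closes by saying that, on these assumptions, "it is estimated that 510 events will be required for the final analysis". It mentions no interim analysis, one-sided test or second hazard ratio. The Follow-up section has each patient followed to 10 years from randomization. The article gives neither the length of accrual nor a calendar date for the final analysis.

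**The concern.** In a time-to-event comparison under proportional hazards, the number of events sets the power. That number depends on alpha, power, the allocation ratio and the hazard ratio, and all four are stated. It does not depend on accrual, length of follow-up or dropout, which decide only when the events arrive. An event count described as required can therefore be checked exactly, and 510 looks too low for a hazard ratio of 0.79.

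If the final analysis is made at 510 events, the trial runs a higher risk than stated of missing a true gain of 5 percentage points. A negative result would then be read as coming from a trial with 80% power. A statistical analysis plan that copies the figure would inherit the error.

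**Working it through.** **Inputs, all from the protocol article:** 5-year DFS 73% (control) and 78% (experimental); hazard ratio 0.79; two-sided alpha 0.05, so z = 1.960; power 80%, so z = 0.842; allocation 1:1.

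**1. The hazard ratio is reproduced.** Under exponential DFS, HR = ln(0.78)/ln(0.73) = 0.7895, which rounds to the stated 0.79. The rates and the ratio agree.

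**2. Events required (Schoenfeld).** d = 4(1.960 + 0.842)² / (ln HR)² = 31.40 / (ln HR)².

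- HR 0.7895: ln HR = −0.2364, d = 561.9, rounded up to 562.
- HR 0.79: ln HR = −0.2357, d = 565.02, strictly rounded up to 566.

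**3. Events required (Freedman).** d = (1.960 + 0.842)² × [(1 + HR)/(1 − HR)]².

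- HR 0.7895: 567.2, rounded up to 568.
- HR 0.79: 570.3, rounded up to 571.

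The plan's 510 is not reproduced. The shortfall against Schoenfeld is 562 − 510 = 52 to 566 − 510 = 56 events, about 10%.

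**4. Power at 510 events.** Schoenfeld: Φ(√510/2 × |ln HR| − 1.960).

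- HR 0.7895: Φ(11.29 × 0.2364 − 1.960) = Φ(0.709) = 76.1%.
- HR 0.79: 75.9%.
- Freedman's version: 75.7% and 75.5%.
- Simulated log-rank test (1650 patients, assumed 4-year accrual, 2000 runs): 76.7% at 510 events and 79.8% at 562. The Monte Carlo standard error is about 1 point, so this agrees with the formulas.

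**5. Attempts to recover 510.**

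| Variant | Events |
|---|---|
| HR 0.785, lower end of what rounds to 0.79 (Schoenfeld) | 536 |
| HR 0.795, upper end (Schoenfeld) | 597 |
| One-sided 0.05, 80% power | 443 to 450 |
| Two-sided 0.05, 90% power | 753 to 764 |
| One-sided 0.05, 90% power | 614 to 623 |
| Lachin–Foulkes exponential test, two-sided, 80% | about 569 to 570 |
| HR 0.78, two-sided, 80% (Schoenfeld / Freedman) | 509 / 514 |

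Only a hazard ratio of 0.78 gives 510, and the plan states no such ratio.

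**6. Can the higher target be reached?** At constant hazards, 10-year DFS is 0.73² = 0.533 and 0.78² = 0.608. With 825 patients per group and no dropout, the expected events by 10 years are 825 × (0.467 + 0.392) ≈ 708. With an assumed exponential dropout of 10% by year 5, the figure is about 645. Both exceed 566. Moving from 510 to 562 events with 1650 patients takes about 0.8 to 1.2 years, assuming uniform accrual over 3 to 6 years and dropout of 0 to 10% by year 5.

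**7. Dropout inflation.** 1500 × 1.10 = 1650, but 1650 × 0.90 = 1485. To keep 1500 after 10% loss takes 1500/0.90 = 1667 patients. The planned 1650 covers a loss of 1 − 1500/1650 = 9.1%.

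**The case against.** The best defence is that 510 may be a forecast and not a requirement. In 1500 patients with an assumed 5 years of accrual and 5 further years of follow-up, about 512 events would be expected. The article gives no lock rule, so treating 510 as the trigger for the analysis is an inference. Follow-up to 10 years could also yield 645 to 708 events, at which power would be about 85% to 88%. On this view the design can deliver 80% power and the fault is one of wording. The loss is also only about 4 points of power, type I error is untouched, and the dropout point concerns 17 patients in 1667.

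Part of this stands. The origin of 510 is unknown, and the shortfall belongs to an analysis at 510 events, not to the number of patients or the planned length of follow-up. The dropout point is small: if the analysis is event-driven, it affects timing only.

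The contradiction remains. The sentence calls the events required for the final analysis and ties them to the assumptions just listed. If 510 is really an expected count, the sentence mislabels it, and an analysis at that count still has about 76% power. An interim analysis, of which none is mentioned, would normally raise the requirement, not lower it.

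**Conclusion.** The concern holds. With the stated rates, hazard ratio, alpha, power and allocation, the requirement is 562 to 566 events by Schoenfeld (568 to 571 by Freedman), and 510 events give about 76% power. The type II error is about 24%, against the stated 20%. This rests on proportional hazards and a standard two-sided log-rank comparison; exponential DFS is needed only to derive 0.7895 from the 5-year rates, and the stated 0.79 leads to the same conclusion. The time needed to reach a higher target rests on assumed accrual and dropout. The 10% dropout inflation is a separate, minor slip of about 1%.

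**What to change.** First trace how 510 was obtained: from a hazard ratio of 0.78, as an expected count under unstated accrual and follow-up, or otherwise. Then make one of two changes in the sample size section, and carry it into the statistical analysis plan:

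- Set the target for the final analysis at 562 events (566 if the rounded ratio of 0.79 is the design value), keeping 1650 patients and the 10-year follow-up. This adds no patients and delays the final analysis by about one year (0.8 to 1.2 under the assumptions above).
- Keep 510 events and state the power as about 76%. This costs only a less favourable published figure.

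If 510 was meant as a forecast, say so, give the accrual and follow-up behind it, and state the required number separately. In the same edit, note that 1650 covers a dropout of 9.1%, or that 10% would call for 1667. The Trial status section describes accrual as ongoing, so on that account the correction can be made before the final analysis.

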### Ethics

The trial was approved by the fudan university shanghai cancer center ethics committee (2108241-22). The study is registered in ClinicalTrails.gov (NCT04320979).

### Trial status

Patient accrual was started on September 1, 2021 and is currently ongoing.

## Discussion

In the current report, we present the protocol of the SUCLANODE trial, which aims to investigate whether adding the posterolateral SCL irradiation to medial SCL irradiation improves DFS in high-risk breast cancer patients after breast surgery. SCL irradiation is widely used for patients with high-risk breast cancer treated with mastectomy and breast-conserving surgery. However, the optimal SCL target volume has been controversial in recent years, high-level data directly comparing entire versus medial SCL irradiation in high-risk breast cancer patients treated with surgery is lacking.

For high-risk patients with less than N3c disease receiving modern adjuvant systemic therapy and radiotherapy, the risk of posterolateral SCL recurrence may be quite low. In our prior retrospective study comparing medial versus entire SCL irradiation in 544 patients with clinical or pathologic N2-N3b disease after breast surgery, only 2 patients (0.4%) had posterolateral SCL recurrence, including 1 who received entire SCL irradiation and had in-field recurrence. Entire SCL irradiation did not significantly improve SCL control and DFS compared to medial SCL irradiation [17]. Another study by Bazan et al. reported a similarly low 0.4% rate of posterolateral SCL recurrence (1/268) in high-risk breast cancer patients treated with IMRT (168 patients) or 3D-CRT technique (72 patients) [20]. In that study, all CTVs were delineated according to the RTOG breast contouring atlas consensus, thus only the medial SCL region was irradiated. None of the patients in the IMRT group had posterolateral SCL recurrence, indicating a very low risk of recurrence in that region even unintentionally excluded from IMRT treatment volumes in those high-risk patients. The one patient with posterolateral SCL recurrence was treated with 3D-CRT technique, which delivered a mean dose of 4647 cGy to the posterolateral SCL region. This evidence suggests posterolateral SCL recurrence after adjuvant RNI may not be attributable to inadequate target volume coverage.

The biophysical effects of radiotherapy are not tumor-specific and can also cause toxicity due to exposure of surrounding normal tissues. The toxicity is of particular concern in breast cancer as more patients become long-term survivors due to advances in systemic and local therapies. Expanding the SCL target volume will inevitably increase neck and shoulder radiation dose, potentially heightening acute and late normal tissue toxicity and reducing quality of life. Bazan et al. found 3D-CRT technique delivered significantly higher incidental dose to the shoulder and back versus IMRT technique, with a tend toward reduced q-DASH scores indicating less shoulder morbidity in patients treated with IMRT technique (*p* = 0.078) [20]. Our prior study also observed a significantly higher rate of pain in the E-SCLI group compared to M-SCLI (26.6% vs. 15.1%, *p* = 0.005) [17]. In this trial, we will evaluate shoulder function via q-DASH questionnaire, patients-reported shoulder/back symptoms, and quality of life. Additionally, a previous study showed 3D-CRT technique delivered significantly higher incidental radiation dose to the posterolateral SCL region than IMRT technique (46.7 Gy vs. 30.2 Gy *P* < 0.0001) when treating medial SCL region based on RTOG consensus [20]. We will utilize advanced IMRT, VMAT, or tomotherapy techniques instead of 3D-CRT technique to minimize incidental irradiation to the posterolateral SCL region in the M-SCLI arm.

